## DISCUSSION

ELECT-TDCS will be the largest trial to date assessing the efficacy of tDCS and the first designed to specifically compare the efficacy of tDCS with a full dose of escitalopram. Demonstrating that tDCS presents efficacy similar to that of a pharmacological treatment is important, because antidepressant drugs present several relative and some absolute contraindications against use. Therefore, tDCS could increase the therapeutic arsenal for use among depressed patients who cannot or are not willing to use antidepressant drugs, e.g. pregnant women,^86^ HIV patients^87^ and patients presenting clinical conditions in which the pharmacokinetic interactions are problematic.^88^

Our study is also interesting from a cost-efficacy perspective, since tDCS is an affordable, portable and ease-to-use therapy. The cost of antidepressant therapy consisting of tDCS might, in fact, be comparable to that of antidepressant drugs, if it is taken into consideration that one tDCS device can be used to perform several applications per day and that one operator can deliver tDCS to two to three patients simultaneously. Finally, tDCS is a technique with few adverse effects.^10^ There are at present no reports of seizures or other severe life-threatening events. The most serious adverse effect reported hitherto is skin burn at the application site, and this has been an uncommon finding.^89^

Another key aspect of ELECT-TDCS is that several biomarkers will be assessed in a multimodal approach. tDCS does not seem to induce peripheral effects in cases of depression, such as changes to blood neurotrophic factors.^77^^,^^90^^,^^91^ However, it increases central neuroplasticity as indexed by paired associative stimulation,^92^ modulates cortical activity as indexed by electroencephalography^93^ and improves working memory and affective processing.^94^^,^^95^^,^^96^ Finally, since the same analyses will be performed in the escitalopram group, we will also explore whether the biological predictors and mediators are different between tDCS and escitalopram responders.

Our study protocol was designed by drawing on our experience from our earlier SELECT-TDCS trial and other advances observed in the field. The choice of using escitalopram at a dose of 20 mg/day represents an advance over the 50 mg/day dose of sertraline used in SELECT-TDCS. The decision to increase the total number of sessions from 12 to 22 was based on findings from a meta-analysis^24^ that suggested that a higher tDCS “dose” would be associated with a larger improvement in depression. Other changes in relation to SELECT-TDCS include: a longer wash-out period to ensure that the subjects were truly “antidepressant drug-free”; an increase in the maximum age of participants in order to improve recruitment; use of automated tDCS devices for sham stimulation, so as to improve blinding; a longer study duration to address the effects of tDCS over a longer time frame; and use of HDRS-17 (instead of MADRS) as the primary outcome measurement, given that in SELECT-TDCS, HDRS-17 presented lower variance and greater psychometric validity (Cronbach’s alpha and intraclass correlation) than MADRS, and was also more sensitive towards detecting between-group differences (data not published).

Nonetheless, most aspects of the SELECT-TDCS trial were maintained, such as recruitment of unipolar depressed patients with different degrees of refractoriness in an acute episode of at least moderate severity; enrollment of antidepressant-free patients; inclusion of patients using benzodiazepine drugs, since we considered that exclusion of these patients could harm recruitment and, in fact, be ineffective given that participants can retain information regarding use of these drugs; bilateral (left-right) DLPFC stimulation; and comparison with a placebo arm, which is crucial, given that as the efficacy of active versus sham tDCS is still under investigation.

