Our secondary aims are to explore the clinical improvement in terms of response status (more than 50% of improvement from baseline to endpoint) and remission status (HDRS-17 ≤ 7 at endpoint). We will also explore improvement in depression using the MADRS and the BDI. Finally, we will also investigate whether any early improvement (week 3) was observed between the groups.

We also aim to identify several predictors and mediators of tDCS response, as described below.

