Motor cortical excitability for tDCS has been used since the reappraisal of tDCS by Nitsche and Paulus in 2000.^11^ Currently, one important line of tDCS research involves measurement of motor cortex excitability after use of tDCS in combination with psychoactive drugs.^59^ This procedure allows indirect measurement of the GABAergic activity (ICI and CSP) and glutamatergic activity (ICF) of the motor system.^60^ These neurotransmitters are involved in the pathophysiology of depression.^61^ Recent studies observed that in relation to healthy subjects, the ICI, ICF and CSP indices are altered in depressed subjects,^62^^,^^63^^,^^64^ although their role as predictors of antidepressant response was not sufficiently investigated.Brain imaging by means of MRI will be collected in approximately half of the sample (120 patients) at baseline and endpoint, and this imaging will include voxel-based morphometry (VBM), diffusion tensor imaging (DTI) and resting-sate functional MRI. Regarding VBM, one consistent finding observed in depressed patients is that the volume of the grey matter in the prefrontal and anterior cingulate cortex bilaterally is lower,^65^^,^^66^^,^^67^ and that there is an increase in gray matter in the left DLPFC after successful antidepressant treatment.^68^ These brain areas will be explored as predictors of tDCS response. On DTI, the fractional anisotropy (FA) of the prefrontal cortex (bilaterally), right temporal lobe and right fusiform gyrus were found to be lower in MDD patients.^69^ Studies on repetitive TMS found an increase in FA in the left frontal-medial gyrus after successful antidepressant treatment,^70^^,^^71^ and these regions are explored in our study. For resting-state fMRI, we explore changes in the default-mode network (DMN) and anticorrelated network (AC) after tDCS treatment. Previous studies observed that depressed patients present greater DMN activity and lower AC activity^72^ and that antidepressant treatment can change the brain activity of these regions.^73^

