According to this formula, for *f* = 0.5, k_p_ is 0.69. Therefore the optimal proportion for allocation between the groups is 1:1:0.69, or approximately 3:3:2, as used in ELECT-TDCS.

We estimated our sample size in accordance with the suggestion of Pigeot et al.^31^ for non-inferiority, triple-arm trials:

$$N_{arm}\geq {\left(t_{1-\alpha ,\;3n-3}\;+\;t_{1-\beta ,\;3n-3}\right)}^{2}*(1+f^{2}+{\left(1-f\right)}^{2})\;{*\left[\left(\sigma /\;{µ}_{DRUG}-{µ}_{PLACEBO})/(r-f\right)\right]}^{2*}$$

This formula shows that the sample size is a product of three factors (in parentheses). The factor in the first parentheses take into account the values of α and β, which were, respectively 0.025 (one-tailed) and 0.2. The factor in the second parentheses is the *f* value (the higher the *f* value is, the larger the necessary sample size will be), which was determined as 0.5 for our study. The factor in the last parentheses involves the standard deviation and effect sizes of the interventions. We took the value of the standard deviation to be a function of the difference in efficacy between the active comparator and the placebo:^31^

$$\sigma =\varepsilon \;({µ}_{DRUG}-{µ}_{PLACEBO})$$

The ε value indicates that the standard deviation is associated with the mean difference values observed in the study. It ranges from 0.2 to 2, and values > 1 are considered conservative. In the present study, we took the ε value to be 1.5, i.e. the standard deviation would be 1.5 times the value of the difference in efficacy between the active intervention and the placebo, which is compatible with depression studies in which the variance is usually high.^†^

Therefore, considering an attrition rate of 13% (similar to SELECT-TDCS), β = 0.2, α_one-tailed_ = 0.025, *f* = 0.5 and ε = 1.5, a total sample of 240 patients will be necessary in order to reject our null hypothesis. For 3:3:2 randomization, this means that in the end, 90, 90 and 60 patients will be respectively allocated to the tDCS, escitalopram and placebo groups.

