### Statistical analysis

In accordance with the recommendations of Pigeot et al.^31^ and Rothmann et al.,^79^ we use a modified *t* test to address our primary study hypothesis (i.e. that tDCS is non-inferior to escitalopram). A *t* test involves obtaining a T value, which should be higher than (in a one-tailed test, as in our study) or different to (in a two-tailed test) a critical *t* value. The T value is obtained by dividing the difference in the means by the mean error (obtained according to the variance and sample size). For this analysis, the T value will be obtained as follows:

$$T=({µ}_{tDCS}-0.5{µ}_{PLACEBO}-0.5{µ}_{DRUG})/\sigma \surd (1/n_{TDCS}+0.25/n_{DRUG}+0.25/n_{PLACEBO})$$

or

$$T=7.44({µ}_{tDCS}-0.5{µ}_{PLACEBO}-0.5{µ}_{DRUG})/\sigma (considering\;that\;the\;n\;values\;are\;known)$$

This T value should be higher than the critical *t*, which for a one tailed α of 0.025 and 237 (N-3) degrees of freedom would be 1.97.

We will also perform exploratory analyses to identify whether a significant difference between the groups is observed over time. Therefore, we will perform mixed-model analyses of variance (ANOVAs) with one independent, within-subject variable (time, with three levels: baseline, week 3 and endpoint) and one independent, between-subject variable (group, with three levels). The dependent variables will be the scores from HDRS, MADRS or BDI. To determine whether a statistical significance is observed at a two-tailed p value of 0.05 or less, post-hoc analyses will be performed to analyze the main and interaction effects of our interventions. Exploratory analyses will also be performed to identify the influence of clinical, demographic and biological variables on the outcome. In addition, logistic regressions will be performed using response or remission as dependent variables and the group as an independent variable. Adverse effects will be assessed by counting the number of events in each group at each evaluation time. The chi-square test will be used to compare the frequency of adverse effects between the treatment groups.

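### The only between-treatment biomarker comparison the article states is set among responders; for baseline markers, a marker-by-arm interaction in all randomised patients answers the question better at almost no cost

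*Protocol article*

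**What the plan says.** Four places in the protocol article bear on this.

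- **Methods, Overview** sets the aim: "We also aim to identify several predictors and mediators of tDCS response, as described below". It also defines "response status (more than 50% of improvement from baseline to endpoint", so being a responder is known only after randomisation and treatment.
- **Methods, Procedures** (list of biomarkers) says of the morphometric imaging regions: "These brain areas will be explored as predictors of tDCS response". Imaging is planned in "approximately half of the sample (120 patients").
- **Statistical analysis** says: "Exploratory analyses will also be performed to identify the influence of clinical, demographic and biological variables on the outcome". It names no arm and no response group to be left out.
- **Discussion** adds a between-treatment step: "we will also explore whether the biological predictors and mediators are different between tDCS and escitalopram responders". It presents this as a further step, made possible "since the same analyses will be performed in the escitalopram group".

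The Limitations section declares the multimodal analyses exploratory. Nowhere does the article describe a marker-by-arm contrast against placebo.

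**The concern.** The useful question about a marker is whether it changes the benefit of tDCS, against placebo or against escitalopram. A comparison of tDCS responders with escitalopram responders approaches this indirectly. It conditions on an outcome that treatment affects, so the two groups are no longer randomised groups. It reduces HDRS-17 to a yes/no status and uses only the patients on one side of the cut. It also makes no use of the placebo arm, the one group that shows what a marker predicts without either active treatment.

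At stake is the reading of the biomarker results: a real differential marker may be missed, and a marker of general prognosis may be described as specific to one treatment. The primary non-inferiority test is not touched.

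**Working it through.** The article gives no figure for this comparison, so there is nothing of its own to reproduce. Marker correlations, response rates and marker prevalence below are assumptions; only the patient numbers come from the article.

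**1. Patients used.** Design and sample size determination gives "90, 90 and 60 patients will be respectively allocated to the tDCS, escitalopram and placebo groups". At assumed response of 30% to 50% in both active arms, the comparison uses 180 × 0.30 = 54 to 180 × 0.50 = 90 of 240 patients (22.5% to 37.5%). If the 120 imaging patients also split 3:3:2, there are 45 per active arm, and 90 × 0.30 = 27 to 90 × 0.50 = 45 are used.

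**2. What it estimates.** Take a binary baseline marker with prevalence q, independent of arm by randomisation. Let t1, t0 be response with and without the marker under tDCS, and e1, e0 the same under escitalopram. The marker odds among tDCS responders are q·t1 / [(1 − q)·t0], and similarly for escitalopram. Their ratio is

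OR = (t1/t0) / (e1/e0).

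q cancels and placebo does not appear. The comparison therefore carries information on differential prediction against escitalopram, and on nothing else.

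| Assumed pattern | tDCS | Escitalopram | Placebo | Responder OR | tDCS/placebo ratio, marker + and − |
|---|---|---|---|---|---|
| A. Predicts benefit of both actives | 60/30 | 60/30 | 25/25 | 2/2 = 1.0 | 2.4 and 1.2 |
| B. Prognostic only | 60/30 | 60/30 | 40/20 | 2/2 = 1.0 | 1.5 and 1.5 |
| C. tDCS gradient only | 60/30 | 45/45 | 25/25 | 2/1 = 2.0 | 2.4 and 1.2 |
| C′. As C, other placebo pattern | 60/30 | 45/45 | 40/20 | 2/1 = 2.0 | 1.5 and 1.5 |
| D. Escitalopram gradient only | 45/45 | 60/30 | 25/25 | 1/2 = 0.5 | 1.8 and 1.8 |

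(Entries are % response with/without the marker.) A and B give 1.0, as does a marker that predicts nothing. C and C′ both give 2.0, although on the ratio scale the marker modifies the tDCS effect in C and not in C′. D gives a difference for a marker unrelated to response under tDCS.

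**3. Efficiency.** Take a continuous standard-normal marker with correlation r = 0.45 with improvement under tDCS and 0 under escitalopram, 90 per arm, 50% response in both, two-sided 5%.

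- *Responders only* (45 per arm). With response at 50%, the mean marker value in tDCS responders is r·φ(0)/0.5 = 0.45 × 0.798 = 0.359, and its variance is 1 − 0.45² × 0.798² = 0.871. In escitalopram responders these are 0 and 1. SE = √[(0.871 + 1)/45] = 0.204; 0.359/0.204 = 1.76; power ≈ Φ(1.76 − 1.96) = 42%.
- *Interaction on the continuous score.* The slope difference is 0.45 and the residual variances are 1 − 0.45² = 0.7975 and 1. SE = √[(0.7975 + 1)/90] = 0.141; 0.45/0.141 = 3.18; power ≈ Φ(3.18 − 1.96) = 89%.

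Simulation with 3000 replicates gives 42% and 88%.

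**4. False positives.** For a purely prognostic marker (same r in both arms), the mean in responders is r·φ(z)/p, where p is the response rate and z its normal quantile. The factor φ(z)/p is 1.058 at 35%, 0.966 at 40%, 0.798 at 50% and 0.644 at 60%. The spurious difference between responder groups is then:

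- r = 0.5, 35% v 60%: 0.5 × (1.058 − 0.644) = 0.21 SD
- r = 0.3, 40% v 50%: 0.3 × (0.966 − 0.798) = 0.05 SD

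| r in both arms | Response | Responder-only, falsely positive |
|---|---|---|
| 0.5 | 35% v 60% | 17% |
| 0.5 | 40% v 50% | 7% |
| 0.3 | 35% v 60% | 9% |
| 0.3 | 40% v 50% | 5% |

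The interaction test stays at about 5%. A repeat run agreed with these figures, and with those in step 3, within one percentage point.

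**The case against.** The strongest reply is that one closing Discussion sentence is not the biomarker plan. It is marked as an extra step, after the same analyses have been done in the escitalopram group. Statistical analysis relates biological variables to outcome with no restriction to responders and no exclusion of placebo. A reader might infer that the biomarker work as a whole drops non-responders and placebo, or that predictors are sought in the tDCS arm alone; the article supports neither. That a marker merely prognostic at r = 0.3 would be flagged in 90 tDCS patients with 82% probability is therefore no criticism of anything the article states.

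The sentence can also be read as asking whether what predicts response differs by treatment, which is the right question. It names no test. In Procedures, the article reports earlier genotype results as larger active-sham differences, so the authors know the placebo-referenced quantity. Detailed models belong in an analysis plan that is not shown.

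Most of this stands, and it limits the reach and severity of the point. It does not remove it. The sentence names the two groups to be compared, and they are responders. Relating a biological variable to outcome is, without an interaction term, a prognostic question. If the authors mean differential prediction, the sentence should say so. Exploratory status governs how much weight a result bears; it does not make a comparison answer a different question.

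**Conclusion.** The point holds in limited form and is minor. Carried out as worded, the responder comparison conditions on a post-randomisation outcome and is an inefficient test of differential prediction: about 42% power against 88%, under the assumptions in step 3. By itself it cannot show that a marker predicts response to tDCS, because its odds ratio does not involve placebo and equals 1.0 both when a marker predicts equally in the two active arms and when it predicts in neither.

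A reader might go further and infer a serious false-positive problem. The figures do not support that in general. The 17% needs a strong prognostic marker and clearly unequal response rates; under moderate values the rate is close to nominal. The article gives neither response rates nor marker correlations, so none of these figures is a forecast for this trial. The loss of power does not depend on unequal response rates. The identity in step 2 applies to baseline markers and does not extend to mediators measured after baseline.

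**What to change.** For baseline markers, replace the responder-versus-responder comparison with a linear model for endpoint HDRS-17 in all randomised patients who have the marker. Include baseline HDRS-17, arm, marker and arm-by-marker terms. Report two interaction contrasts: tDCS v placebo (does the marker modify the effect of tDCS?) and tDCS v escitalopram (does it predict differently between the two?). Call a marker a predictor of tDCS response only if the placebo contrast supports it; a marker related to outcome without that support should be called prognostic.

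This changes analysis wording only and needs no extra patients, samples or visits. The cost is that fewer markers will qualify. The placebo contrast rests on 90 + 60 = 150 patients at most, and on fewer in the imaging subset, so estimates with confidence intervals will say more than significance alone.

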### Limitations

ELECT-TDCS also presents some limitations. First, tDCS is being compared with escitalopram and therefore the results will not be fully generalizable to other antidepressant drugs. Second, we are not testing other tDCS montages and parameters that have also improved depressive symptoms. Third, we are not testing the combination of tDCS with pharmacotherapy or cognitive-behavioral therapy. Finally, our multimodal analyses are exploratory.

## CONCLUSIONS

The ELECT-TDCS trial is a 10-week, phase-III, non-inferiority, triple-arm, placebo-controlled study that is investigating whether tDCS is non-inferior (i.e. whether it has similar or superior efficacy) to 20 mg/day of escitalopram. The results from our trial have the potential to introduce a novel technique into the therapeutic arsenal for depression treatment, particularly in primary care contexts or among patients who cannot tolerate or are not willing to use antidepressant drugs. Our multimodal investigation of biomarkers will also contribute towards understanding the antidepressant mechanisms of the effects of tDCS.
